# Effects of Integrating Family Planning With Maternal, Newborn, and Child Health Services on Uptake of Voluntary Modern Contraceptive Methods in Rural Pakistan: Protocol for a Quasi-experimental Study

**DOI:** 10.2196/35291

**Published:** 2022-03-08

**Keywords:** family planning, integrated health services, contraceptive prevalence rate, modern contraceptive prevalence rate, modern contraceptive method, rural Pakistan

## Abstract

**Background:**

The uptake of modern contraceptive methods (MCMs) remains low, with 25% of women reporting their use in Pakistan. The overarching interventions covering service delivery platforms at facility and community levels necessitate the integration of family planning (FP) with maternal, newborn, and child health (MNCH) services.

**Objective:**

The main aim of this study is to evaluate the impact of an integrated FP-MNCH service delivery model to increase coverage of MCMs in rural Pakistan. Moreover, we aim to measure the level of effectiveness of interventions regarding the uptake of MCMs.

**Methods:**

A quasi-experimental, sequential, mixed methods study design with pre- and postevaluation will be adopted to evaluate the impact of integration of FP with MNCH services. The interventions include the following: (1) capacity strengthening of health care providers, including technical trainings; training in counseling of women who attend immunization centers, antenatal care (ANC) clinics, and postnatal care (PNC) clinics; and provision of job aids; (2) counseling of women and girls attending ANC, PNC, and pediatric clinics; (3) ensuring sustained provision of supplies and commodities; (4) community engagement, including establishing adolescent-friendly spaces; and (5) use of District Health Information System data in decision-making. Descriptive statistics will be used to estimate prevalence (ie, proportions) and frequencies of outcome indicators. A univariate difference-in-difference analytical approach will be used to estimate the effect of the interventions. In addition, a Blinder-Oaxaca decomposition analysis will be conducted to identify and quantify determinants of the modern contraceptive prevalence rate.

**Results:**

The intervention phase began in July 2021 and will run until June 2022. The impact assessment will be conducted from July to September 2022.

**Conclusions:**

This project will evaluate the impact of integrating FP with MNCH services. Furthermore, this study will identify the drivers and barriers in uptake of MCMs and will simultaneously help in modifying the interventional strategies that can be scaled up through existing service delivery platforms within the public and private sectors, according to the local sociocultural and health system context.

**Trial Registration:**

ClinicalTrials.gov NCT05045599; https://clinicaltrials.gov/ct2/show/NCT05045599

**International Registered Report Identifier (IRRID):**

DERR1-10.2196/35291

## Introduction

### Background

The scaling up of family planning (FP) programs has yielded a multitude of benefits in terms of improving health outcomes and paving opportunities for poverty reduction and women’s empowerment. FP programs have effectively contributed to a significant reduction of 32% of all maternal deaths and 10% of all child deaths. Moreover, these programs enhance women’s empowerment and gender equity, and, within that, they are aimed at achieving a higher level of universal female primary education. Over the past four decades, FP programs have led to a globally increased contraceptive prevalence rate (CPR), from 10% to 60%, and a substantial reduction in fertility rate from 6 to 3 children per woman in low- and middle-income countries [1,2].

Modern contraceptive methods (MCMs), such as condoms, contraceptive pills, injectables, and intrauterine devices, serve as significant measures of fertility control [1]. There is a strong body of evidence suggesting that providing a woman with opportunities to opt for the MCM of her choice through a continuum of care is viable and cost-effective, not only at the individual level but also at the broader health system level [2,3].

In Pakistan, FP programs started in the mid-1960s [1]. Later, a Lady Health Worker (LHW) outreach program was initiated in 1994, which primarily focused on FP services at the national level. Pakistan has been a signatory on various international commitments to improve access to reproductive health services, including the following: (1) the Millennium Development Goals (2000), aimed at increasing the CPR from 12% in 1990 to 55% in 2015 [4]; (2) the London Summit on Family Planning 2012, aimed at raising the CPR to 55% by 2020; and (3) the Sustainable Development Goals (2015), aimed at achieving universal access to reproductive health services by 2030. Pakistan has made considerable progress over time, yet these targets have not been fully reached [5].

Generally, the provincial government’s Population Welfare Department and the Department of Health are both responsible for translating the government’s vision of health and FP. However, the Department of Health has lagged behind in taking ownership of the FP agenda to fully optimize the resources to achieve the objectives [6]. The government’s FP2020 agenda invigorated efforts to accelerate progress in achieving higher use of MCMs. Political commitment at the national level and at the Sindh province level culminated in appointing the same minister to the Department of Health and the Population Welfare Department to ensure functional integration in both departments. Moreover, the FP2030 Secretariat has been created to bring all stakeholders onto a single platform and provide facilitation for nongovernmental organizations (NGOs) and private sector entities that are working in the FP arena.

Several collaborative initiatives have contributed to increased MCM uptake in Pakistan, as demonstrated by a nearly three-fold increase in the CPR from 13% to 34% between 1990 and 2018 (0.5% annual increment) [7-9]. However, there still remains a large unmet need for FP, toward which progress has been slow and in some cases stagnant.

A review of the existing data report low use of MCMs at 25% among women aged 15 to 49 years and 7% among adolescents aged 15 to 19 years in Pakistan [7]. This indicates a high unmet need of FP, specifically among currently married women (17%). For example, out of all pregnancies in Pakistan, 46% are unintended and unsafe, and the abortion rate remains high at 50 per 1000 women [7]. It is noteworthy that 78% of nonusers of MCMs are women aged 15 to 49 years who have never had discussions regarding FP methods with any health care provider at the community or facility levels [7]. Further, of those who give birth, many do not receive (1) standard antenatal care (ANC), postnatal care (PNC), or quality services at the time of delivery or (2) appropriate management for mother and newborn complications [10].

This is the result of various barriers that have evolved within the broader political, social, and cultural context of Pakistan. A deeper understanding of these barriers and determinants is required to identify gaps within the health system and expand the coverage of FP and maternal, newborn, and child health (MNCH) services [1,11]. From the demand side, literature suggests that women’s empowerment, gender equality, and religious obstacles are contributing factors that heavily influence the uptake of contraceptive methods [12]. However, a further exploration is required at the local level in terms of community perspectives of, resistance to, and attitudes toward FP and contraceptive uptake. Within the country, people living in the lower wealth quintiles (below 25%) and residing in rural areas have a lower literacy level, with young women experiencing a great unmet need for FP services and products [13]. This has translated into poor acknowledgement and adoption of practices relating to healthy timing and spacing of pregnancies and, consequently, higher fertility rates [14,15]. Preference for sons and a lack of husbands’ participation also count as prominent factors in the context of Pakistan that present key barriers to the uptake of FP methods [16,17]. Studies further report that the involvement of supportive male family members has effectively increased the rate of voluntary uptake of contraceptive methods [17]. Given that the bulk of Pakistan’s population is comprised of youth, the need for adolescent-focused interventions to evaluate and improve reproductive health outcomes at scale is urgently needed [8,18].

On the supply side, the literature reports lack of access to information; lack of access to health care service delivery points, especially in rural communities; and fear of side effects as key barriers to MCM uptake. For those who do adopt an MCM, method discontinuation due to poor quality of services provided, attitudes of health care providers, and cost-bearing during treatment of side effects [9,13,18,19] are key factors in low contraceptive prevalence. Considering FP as the major factor in improving health indicators throughout the course of women’s and children’s lives [20], thereby building trust in government services, making needs-based alignment of FP programs in the country would substantially affect the resistance to opting for contraception [21].

Given these barriers, designing and evaluating integrated FP programs that are based on needs and delivered through existing service delivery platforms have the potential to improve the health and well-being of women and children in Pakistan. The integration of FP with immunization in Malawi resulted in a 14% increase in the uptake of FP methods. Parents experienced greater feasibility marked by reductions in time lost and transport costs as well as access to greater awareness and knowledge while accessing services on the same day. Similarly, health care providers expressed that this integration enhanced their skills, knowledge, and competence [20]. Similar results were found in Liberia and Rwanda, with an emphasis on maintaining privacy for couples in public health settings. The integration of the immunization schedule, with extended postpartum FP, resulted in an increase in uptake [22,23]. In order for the successful and equity-based implementation of integrated services, it was reported that following standard protocols for provision of care and training of health care providers at facility and community levels was necessary [24].

Moreover, a recent study conducted during the COVID-19 pandemic in Ethiopia examined the integration of FP with maternal health care services, including ANC, delivery, PNC, and immunization. The results showed a 6% increase in the uptake of integrated FP services, which is significant in a low-resource setting, given the widespread effect of the global pandemic [25].

The literature has also shown that interventions focusing on community outreach programs and interpersonal communications increase social acceptance of FP methods [26]. However, home-based counseling alone is not sufficient for the uptake and continuation of FP methods [27]; developing linkages with health facilities, maintaining privacy at a health facility, and delivering services in a socioculturally sensitive manner is also important.

In line with this, efforts have been made that involve facility- and community-level health care providers for the provision of MNCH services as the primary mandate of the National MNCH Program. However, there are still deficiencies at the interfacility and intrafacility levels, for example, (1) a lack of coordination among departments, such as pediatrics and gynecology and obstetrics; (2) a lack of management-level coordination with frontline health workers; (3) a lack of equipment and logistics management manifested as an imbalance in demand and supply; and (4) a lack of overall governing bodies [6,28]. Thus, overarching interventions covering service delivery platforms at facility and community levels necessitate the integration and scaling up of FP and MNCH services.

### Implementation Context

Pakistan is comprised of four provinces (ie, Punjab, Sindh, Khyber Pakhtunkhwa, and Balochistan), two autonomous territories (ie, Gilgit-Baltistan and Azad Jammu Kashmir), and a federal territory (ie, Islamabad); these collectively encompass 150 districts [29]. This study will be conducted in two districts of Sindh province (Figure 1). Sindh has the highest rural-urban difference in fertility rates: 4.7 and 2.9 per woman, respectively. Median age at first birth is 23 years, with only 18% of this age group receiving any contraceptive method. Overall, modern CPR (mCPR) in Sindh is lower (24% vs 26%) and unmet needs are higher (22% vs 17%) as compared to national-level statistics [30].

The public health system consists of a three-tiered health delivery system comprised of domiciliary and outreach services rolled out through LHWs and primary- and secondary-level health care facilities in each district [2]. Each LHW has a catchment population of approximately 1000 to 1500 people. They provide educational, preventive, and promotive services as well as some aspects of curative services in the community. They provide MNCH and FP services to eligible families.

**Figure 1 figure1:**
[figure not shown]
Map of Pakistan showing the districts of Badin (control) and Matiari (intervention) in Sindh province.

### Theoretical Framework

The theoretical underpinning of behavior change will be based on the Theoretical Domains Framework (TDF), version 2.0. The TDF will be applied to provide an in-depth exploration and understanding of factors regarding the demand and supply side and their interaction with and influences on FP uptake [31,32]. This project aims to implement a complex intervention (Figure 2) within health facilities and their catchment communities. This complex intervention includes a series of strategies involving community engagement by extensive community mobilization, availability of trained staff, and sustainable supply of commodities with the required recording and reporting system. Continuous process monitoring and quality assurance will help to replicate the success and address possible barriers during implementation of the intervention. The mechanism of action built on the TDF adopts domains and constructs, including knowledge, skills, beliefs, and intentions. Furthermore, the TDF provides a detailed understanding of complex behavior; thus, it will be used to evaluate the impact of complex interventions and strategies.

**Figure 2 figure2:**
[figure not shown]
Theoretical Framework: integrated FP-MNCH services. ANC: antenatal care; DHIS: District Health Information System; FP: family planning; HCP: health care provider; LHW: Lady Health Worker; MNCH: maternal, newborn, and child health; OPD: outpatient department; PNC: postnatal care; SRH: sexual and reproductive health; VHC: village health committee; WSG: women support group.

### Research Question

The research question that will be answered by this study is as follows: What is the impact of integrating FP with MNCH services on the uptake of voluntary MCMs in a rural district of Sindh province, Pakistan?

### Aim and Objectives

The aim of this study will be to evaluate the impact of an integrated FP-MNCH service delivery model to increase coverage of MCMs in rural Pakistan.

The objectives of this study are as follows:

To gain an understanding of the cultural and health service delivery contexts to inform a socioculturally appropriate and acceptable intervention package scalable in rural PakistanTo implement the intervention package at health facilities and outreach communities through existing public and private sector resourcesTo measure the impact and level of effectiveness of interventions on the uptake MCMsTo identify and quantify the drivers of improved uptake of voluntary methods of FP, especially MCMs.

## Methods

### Study Design

A quasi-experimental, sequential, mixed methods study design with pre- and postevaluation is proposed to assess the impact of implementing an integrated delivery model on the uptake of MCMs in a rural district of Sindh province, Pakistan.

### Ethics Approval

Ethical clearance for this project was sought from the Ethical Review Committee of the Aga Khan University on June 26, 2020. The study protocol was approved by the National Bioethics Committee, Pakistan (ERC number 2021-3606-19065). The baseline assessment was completed in January 2021. The inception period included hiring and deployment of study staff and their training in the standard operating procedures of the project.

### Qualitative Component

#### Overview

The overall objective of the qualitative component is to understand the barriers that married women and girls who are at risk of an unwanted pregnancy face in accessing and using voluntary FP. The information will be used to inform the integrated intervention design and delivery platform. The qualitative component will include focus group discussions (FGDs) with married women of reproductive age (MWRA; 18-49 years) and adolescent girls and boys (15-19 years) to understand behaviors and community-level hindrances to acceptance and use of FP methods. Due to the sensitivity of the topics, separate FGDs will be conducted with male and female participants. In-depth interviews will also be conducted with service providers and health facility managers to understand facility-level and supply-side barriers to uptake of modern FP methods and services (see Multimedia Appendix 1 for sample sizes of FGDs and in-depth interviews).

A purposive sampling technique will be used. We aim to conduct 10 in-depth interviews and two FGDs, with 5 to 6 participants in each group. However, this will depend on reaching the theoretical point of saturation. A thematic approach will be used to analyze the data. The FGD guide for data collection will be based on the TDF.

#### Analysis of the Qualitative Component

Analysis will be done using NVivo software (version 11; QSR International). The TDF will be the guiding framework for coding and thematic analysis.

### Systematic Review

A systematic review of the existing research will be conducted to identify effective FP interventions and strategies that led to an increase in the uptake of MCMs. The research question will look at the impact of effective interventions and strategies on improving the uptake of MCMs in South Asian countries. Various databases (PubMed, Cochrane Database of Systematic Reviews, EBSCO CINAHL, Web of Science, ProQuest Dissertations & Theses, etc) will be used to collect articles published from January 2000 to June 2021. Covidence, a systematic review management program, will be employed to facilitate collaboration across the team. A meta-analysis will be used to synthesize the data from relevant studies into a single quantitative pooled estimate. The pooled estimate will be the outcome of the meta-analysis and will be explained by a forest plot. The meta-analysis will be done using RevMan (Review Manager) software (version 5.4.1; The Cochrane Collaboration). For categorical variables, odds ratios with 95% CIs will be reported; for continuous outcomes, mean differences or standard mean differences with 95% CIs will be reported.

### Quantitative Component

#### Overview

A nonrandomized, quasi-experimental study design with intervention and control arms is proposed to assess the impact of implementing a complex delivery model of interventions on the voluntary uptake of MCMs in two rural districts of Sindh. Two sequential face-to-face household surveys will be conducted before and after the 12-month implementation of the interventions [33]. The surveys will document the changes over time in mCPR alongside other outcomes of interest, such as unmet needs and demands satisfied.

#### Selection of Control District

We used the propensity score matching technique to select the control district (Table 1). This procedure estimates the probability and propensity that a study unit that has not received the intervention is similar at baseline to another unit from the intervention group, based on a set of key characteristics. As such, it reduces the problem of comparison across large numbers of key variables [34]. In the context of our study, this matching was done to select Badin as the control district to compare with the intervention district of Matiari (Figure 1). The variables used in generating propensity score matching included CPR, mCPR, unmet needs, ANC by skilled providers, deliveries by skilled birth attendants, the Human Development Index, and percentage of full immunization coverage. The district-level data of these indicators were taken from the Sindh Multiple Indicator Cluster Survey 2018 for all 23 rural districts (Multimedia Appendix 2).

**Table 1 table1:** Selection of control district using propensity score matching.

District	Unmet needs, %	CPR^a^, %	Modern CPR, %	Fully immunized, %	Deliveries by skilled birth attendants, %	Antenatal care, %	Propensity score
Badin (control district)	17.9	28.1	28.1	45.6	61.9	82.0	0.36
Matiari (intervention district)	25.8	32.4	30.6	68.0	65.5	85.7	0.31

^a^CPR: contraceptive prevalence rate.

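### Badin is presented as a propensity-score match to Matiari, but a score from one treated district with seven covariates adds no demonstrated comparability, and the named effect analysis is unadjusted

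*Protocol article*

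**What the plan says.** In Methods, Selection of Control District, the article writes: "We used the propensity score matching technique to select the control district". It explains the technique as a way to find an untreated unit that resembles the treated one before the intervention, and concludes that "this matching was done to select Badin as the control district", with Matiari as the intervention district.

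On the inputs it says: "The variables used in generating propensity score matching included CPR, mCPR, unmet needs, ANC by skilled providers, deliveries by skilled birth attendants", followed by "the Human Development Index, and percentage of full immunization coverage". The data "were taken from the Sindh Multiple Indicator Cluster Survey 2018 for all 23 rural districts".

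Table 1 prints six of the seven indicators (the Human Development Index has no column) and a score for each of the two districts: Badin 0.36, Matiari 0.31. The article does not name the model behind the score and refers to Multimedia Appendix 2 for the matching.

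Statistical Analysis of the Quantitative Component names one method for the effect of the interventions, a univariate difference-in-difference. The Blinder-Oaxaca decomposition named beside it is for determinants of mCPR, not for the effect.

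**The concern.** A propensity score is estimated by contrasting treated with untreated units. Here there is one treated unit and seven predictors, so the data hold almost no information about what distinguishes treated from untreated districts. Two similar scores from such a model do not show that two districts are alike, and Table 1 shows that on two matching variables they are not.

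Both variables bear on the question. Immunization coverage reflects contact with the maternal and child health platforms through which the intervention is delivered, and unmet need is a secondary outcome. A reader who accepts the matching label will credit the design with a balance it has not shown. The only named effect analysis then makes no covariate adjustment. Any difference between the districts in the background change in mCPR passes one for one into the estimate: each point of divergence is one eighth of the planned effect of 36.9 − 28.9 = 8 points.

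**Working it through.** **Inputs (Table 1).** Order: unmet need, CPR, mCPR, fully immunized, skilled delivery, antenatal care, score.
- Badin: 17.9, 28.1, 28.1, 45.6, 61.9, 82.0, 0.36.
- Matiari: 25.8, 32.4, 30.6, 68.0, 65.5, 85.7, 0.31.
- Units: 23 districts, 1 treated, 7 named covariates.

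**Can the printed scores be reproduced?** No. The covariates of the other 21 districts, the Human Development Index values and the model form are not in the article. What follows is a consistency check under an assumption.

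**1. Balance of the pair (Matiari minus Badin, percentage points).**
- Full immunization: 68.0 − 45.6 = 22.4
- Unmet need: 25.8 − 17.9 = 7.9
- CPR: 32.4 − 28.1 = 4.3
- Antenatal care: 85.7 − 82.0 = 3.7
- Skilled delivery: 65.5 − 61.9 = 3.6
- mCPR: 30.6 − 28.1 = 2.5

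**2. Can the model be estimated?** There is one event for seven covariates, 1/7 ≈ 0.14 events per variable. A finite logistic maximum-likelihood fit exists only if Matiari lies inside the convex hull of the 22 other districts. In 2,000 simulated sets of 23 districts (normal covariates, correlation 0 or 0.5), with the treated district a random draw, there was no finite fit in about 99% of sets with seven covariates and about 97% with six. With the treated district exactly at the covariate centre, this fell to about 4% and 1%. A fit is therefore usually unavailable, but it is likely if Matiari is a typical district.

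**3. What the printed scores would imply.** Assume logistic maximum likelihood with an intercept on these 23 districts. The score equations then require Σp = 1 and, for every covariate, Σp·x = x of Matiari.
- Mean score: 1/23 = 0.043. The printed pair sums to 0.36 + 0.31 = 0.67, leaving 0.33 for the other 21 districts (0.33/21 = 0.016 each on average).
- Score-weighted mean of the other 21 = ((1 − 0.31)·x_Matiari − 0.36·x_Badin) / 0.33.
- Full immunization: (0.69 × 68.0 − 0.36 × 45.6)/0.33 = (46.92 − 16.42)/0.33 = 92.4% (91.4% to 93.6% allowing for rounding of the scores).
- Unmet need: (0.69 × 25.8 − 0.36 × 17.9)/0.33 = (17.80 − 6.44)/0.33 = 34.4% (34.0% to 34.8%).
- mCPR 33.3%, CPR 37.1%, skilled delivery 69.4%, antenatal care 89.7%.

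A weighted mean cannot exceed its largest member. At least one other rural district would therefore need full immunization of 91.4% or more, against 45.6% and 68.0% in the two printed districts. The values for mCPR, CPR, skilled delivery and antenatal care are unremarkable.

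**4. Is a control scoring above the treated district a contradiction?** No. The same equations give Σp·η = η of Matiari for the linear predictor η, so at least one control must score as high or higher. This held in all 300 simulated sets in which a finite fit was obtained.

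**5. Badin's CPR and mCPR.** Both are printed as 28.1, which would mean no use of traditional methods. The corresponding gap in Matiari is 32.4 − 30.6 = 1.8 points. Both figures are model inputs, so an error in either would change the score.

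**The case against.** The strongest reply is that the article is condensed. It names no model, says only that the variables included the seven listed, and sends the reader to an appendix that is not shown. Three stronger readings are tempting, and the documents do not support them.

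- A reader might infer that the printed scores are impossible. They sum to less than 1, the higher control score is expected, and the score equations bind only under an assumed model. If no finite fit existed or another estimator was used, they need not hold.
- A reader might set the implied values against the Sindh averages in Implementation Context (mCPR 24%, unmet need 22%). Those are province-wide figures with their own citation. They cannot contradict a score-weighted mean over rural districts, and both Table 1 districts already exceed 24% mCPR.
- A reader might infer that the design has no protection against confounding. The pair is fairly close on mCPR, antenatal care and skilled delivery, and difference-in-difference removes fixed level gaps. The gaps in immunization and unmet need bias the estimate only if they go with different trends, and the article gives no trend data either way.

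All of this stands. It is also fair that adjusted analyses may be in an analysis plan that is not shown. None of it supports the matching claim itself: one treated district remains too little for a seven-covariate score, Table 1 shows the two large gaps, and the effect analysis that the article does fix is univariate.

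**Conclusion.** The point holds in a limited form. The propensity score adds no demonstrated comparability between Badin and Matiari. The visible imbalance is 22.4 points in full immunization and 7.9 points in unmet need, with the other printed indicators 2.5 to 4.3 points apart. These figures come straight from Table 1 and need no assumption.

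The implied 92% immunization and 34% unmet need rest on an unstated logistic model. They are a reason to re-check the scores against the source data, not proof of error. The identical CPR and mCPR in Badin is likewise a query.

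The univariate difference-in-difference deals with fixed level differences. It does not deal with sample composition that differs or changes between surveys, or with trends related to covariates. The size of any resulting bias cannot be computed from the article.

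**What to change.** Keep Badin as the control.

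- **Selection of Control District.** Re-check the Table 1 scores and Badin's CPR and mCPR against the source data. Replace the claim of a propensity-score match with a description of Badin as a chosen comparator. Report the imbalances, Badin's standardized (Mahalanobis-type) distance from Matiari, and its rank among the 22 candidate districts.
- **Statistical Analysis of the Quantitative Component.** Make the main effect estimate a difference-in-difference adjusted, by regression or weighting, for woman-level covariates that the intervention cannot change: for example age, education, wealth and parity as it stood at baseline, where collected. If regression is used, include the interaction of these covariates with survey round, since main effects alone deal with composition but not with covariate-related trends. Do not adjust for antenatal or postnatal care use, institutional delivery or other outcomes, because that would remove part of the effect. Report the univariate estimate alongside.
- **Limitation to state.** With one district per arm, neither matching nor adjustment can separate district-specific time changes from the intervention effect.

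The cost is a desk re-check, modest extra analysis, possibly some loss of precision if weighting is used, and a weaker claim about the control district. No new district or survey is needed.
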